### Children

The research team will visit all participating schools to give a brief presentation about the study to students in grades 1–6 (ages 6–12). They will distribute a plain language statement and an opt-out form for students to take home to their parents/guardians. Students will be included in data collection unless they or their parent/guardian actively opt-out. Surveys will be conducted at the start (baseline), and after the first, second, and third years of the intervention. All children present on the day of data collection who have not opted out will be eligible. Consequently, the composition of children included in each time point of data collection will vary, with some children being followed longitudinally, while others will not.

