### Outcomes

#### Primary intervention effectiveness outcomes.

The primary measure of intervention effectiveness will be the between-group difference in change over time from baseline to year 3 in childhood z-BMI score in repeat cross-sections of grade 1–6 children in intervention and control schools. Cross-sections will be used because we are measuring the effectiveness of the intervention on the school population and not on individual children. Anthropometric data will be collected at each school by trained members of the research team at baseline (pre GMB1), and after 1, 2 and 3 years (primary endpoint). Height (cm) will be measured using a Charder HM-200P stadiometer and weight (kg) using A&D UC-321 digital scales and BMI (kg/m^2^) will be calculated and compared to the WHO reference population [45].

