### Sample size calculations

Victorian Government Department of Education summary statistics compiled in 2023 indicate that, in the 21 regional and remote LGAs of the Southwestern Department of Education region (excluding schools on the geographical fringe of Melbourne in Brimbank, Melton, and Western Melbourne education areas), there were 57,828 children in primary schools. A total of 47,087 (81.4%) children attended the 147 eligible schools with an average of 320 students per school. By recruiting 28 schools and accounting for a 20% school dropout rate, it is anticipated that data will be collected across all time points (baseline, year 1, year 2 and year 3) in 22 schools. A sample of 22 schools, with approximately 200 participating students per school, will provide 83% power to detect a difference of 0.13 units in the primary outcome (z-BMI) between study groups; assuming z-BMI standard deviation 1.1 and intra-cluster correlation coefficient 0.02, as found in the WHO STOPS trial in a comparable population [22,70]. An effect size of 0.13 units in z-BMI it was shown to be achievable, using similar intervention methods, after 2 years in the WHO STOPS trial. Power was estimated using Shiny CRT calculator based on a cluster randomised parallel design with baseline measure, cross-sectional samples, and exchangeable correlation structure (α = 0.05) [71].

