### Statistical analysis

Students will be the unit of observation for effectiveness analyses and analyses will be conducted under the intention-to-treat principle. The effect of the STAIR intervention on the z-BMI will be assessed using a linear mixed model with study group, time (baseline, year 1, year 2, year 3), and the interaction group × time as fixed effects. School and student will be included as random effects to account for clustering of students within schools and repeated measures in students measured more than once). Secondary outcomes will be analysed by fitting a generalised linear mixed model with link and distribution selected according to the outcome distribution. Whether age modifies the intervention effect will be explored using the same modelling approach including additional interaction terms. The environmental audit, and implementation outcomes will be analysed at the school level using descriptive statistics and thematic analyses.

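### If a child's z-BMI correlates less over longer gaps, the student random effect in the primary model makes the baseline-to-year-3 standard error too small

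*Protocol article*

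**What the plan says.** The Protocol article, under Statistical analysis, specifies a "linear mixed model with study group, time (baseline, year 1, year 2, year 3), and the interaction group × time as fixed effects". The next sentence deals with dependence: "School and student will be included as random effects to account for clustering of students within schools and repeated measures in students". The student effect is therefore the stated means of handling repeated measurements of a child. No random slope, residual correlation structure or robust standard error is named, and none is excluded.

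Under Primary intervention effectiveness outcomes, the primary measure is the "between-group difference in change over time from baseline to year 3 in childhood z-BMI score in repeat cross-sections of grade 1–6 children". Under Children, the article explains that "the composition of children included in each time point of data collection will vary, with some children being followed longitudinally, while others will not". Repeated measurement is thus partial but built into the design, and the primary contrast spans the longest interval available.

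**The concern.** A student random intercept with independent residuals is compound symmetry: one common correlation for any two measurements of the same child. In growing children one would expect z-BMI one year apart to agree more closely than z-BMI three years apart. If so, the single fitted correlation is a compromise set mostly by short gaps. It is higher than the true three-year correlation, and the model claims more precision for the baseline-to-year-3 change than the data hold.

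The estimate itself is not at issue. At stake are its confidence interval, which would be too narrow, and the primary test, which would reject a true null more often than the stated alpha of 0.05.

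**Working it through.** **Inputs from the article.** 28 schools reduced to 22 by dropout (11 per arm at 1:1), about 200 students per school, SD 1.1, ICC 0.02, target difference 0.13, alpha 0.05 (taken as two-sided), four yearly waves, grades 1–6.

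**Assumed, because the article gives no figure.** Within-child correlations at 1, 2 and 3 years; attendance and retention; equal grade sizes; no school-by-year drift unless stated.

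**1. The article's own figure.** It says: "A sample of 22 schools, with approximately 200 participating students per school, will provide 83% power to detect a difference of 0.13 units".
- Variance of a school mean: v = 0.02×1.21 + 0.98×1.21/200 = 0.0242 + 0.0059 = 0.0301.
- Correlation of two school means over time: r = 0.0242/0.0301 = 0.803.
- Variance of the effect: (2/11)·v·(1 − r²) = 0.1818×0.0301×0.355 = 0.00194, so SE = 0.0441.
- Power: Φ(0.13/0.0441 − 1.96) = Φ(0.99), about 83.9%.

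The 83% reproduces. It treats the waves as separate cross-sections, so the within-child correlation does not enter it.

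**2. Which gaps inform the common correlation.** Pairs of waves per grade cohort, by grade progression:

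| Cohort | Waves seen | 1 yr | 2 yr | 3 yr |
|---|---|---|---|---|
| Grades 1–3 at baseline (three cohorts) | 0–3 | 9 | 6 | 3 |
| Grade 4 at baseline | 0–2 | 2 | 1 | 0 |
| Grade 5 at baseline | 0–1 | 1 | 0 | 0 |
| Grade 6 at baseline | 0 | 0 | 0 | 0 |
| Entrants, year 1 | 1–3 | 2 | 1 | 0 |
| Entrants, year 2 | 2–3 | 1 | 0 | 0 |
| Entrants, year 3 | 3 | 0 | 0 | 0 |
| Total (26) | | 15 | 8 | 3 |

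So 23 of 26 pairs are 1 or 2 years apart.

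**3. Direction, by hand.** Take 0.93/0.88/0.83. The pair-weighted mean is (15×0.93 + 8×0.88 + 3×0.83)/26 = 0.903. The variance of a child's three-year change is proportional to 1 − 0.83 = 0.17, but the model would use about 1 − 0.903 = 0.097. For children seen at both ends the SE ratio is roughly √(0.097/0.17) = 0.76. The full model also uses children seen at only one end, so its ratio is a little higher.

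**4. Full calculation.** For each pattern, the school-plus-student random-intercept model was fitted to its best-fitting (expected-likelihood) values. The model-based SE of the year-3 contrast was then compared with its true (sandwich) SE. Type I error = 2×[1 − Φ(1.96 × SE model / SE true)].

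| Correlation at 1/2/3 years | SE ratio, full attendance | Type I, full attendance | Type I, 85% attendance |
|---|---|---|---|
| 0.90/0.90/0.90 | 1.00 | 5.0% | 5.0% |
| 0.90/0.88/0.86 | 0.91 | 7.5% | not run |
| 0.96/0.95/0.94 | 0.89 | 8.2% | 7.9% |
| 0.94/0.91/0.88 | 0.82 | 10.7% | 10.2% |
| 0.93/0.88/0.83 | 0.78 | 12.5% | 11.8% |
| 0.92/0.85/0.78 | 0.76 | 13.5% | 12.7% |

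Example, 0.93/0.88/0.83 at 85% attendance: 0.0175/0.0219 = 0.80, and 1.96×0.80 = 1.57, which gives about 12%. A first-order autoregressive correlation of 0.95 per year gives 13.5–14.0% for yearly retention of 80–100%.

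**5. Simulation check.** REML fits under the null, 1,800 replicates each, 93% yearly retention, 85% attendance:
- flat 0.90: 5.0%;
- 0.95/0.93/0.92: 8.9% (mean model SE 0.0146, actual SD 0.0164);
- 0.90/0.86/0.82: 9.2% (0.0204, 0.0232);
- autoregressive 0.95: 12.7% (0.0161, 0.0206).

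**6. With school-by-year variation.** The article gives no figure for this, so cluster autocorrelations of 0.80–0.95 were assumed. With a school-by-year effect in the model, 0.93/0.88/0.83 falls from 12.5% to 7.5% (at 0.95) and 5.9% (at 0.80). For 0.92/0.85/0.78 the fall is from 13.5% to 8.2% and 6.1%. If the variation exists and is left out of the model, type I error is about 21–58% over the same range, mostly for that separate reason.

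**The case against.** The strongest reply is that a condensed article names random effects at both levels of dependence and leaves covariance structure and type of standard error to the analysis plan. That stands in part. The article does not say intercept only, independent residuals or model-based standard errors, so a reader who infers that it fixes all three goes too far. But the point is not silence. The article states the student effect as its means of handling repeated measures, and a plan that implements that sentence plainly inherits the problem.

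A reader might also infer that type I error is 8–13% as a fact, or that a null intervention would be declared effective twice as often as intended. The documents do not support that. They give no within-child correlation, decay or retention, and a flat correlation gives exactly 5%.

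Nor is the inflation a fixed amount, independent of school-level drift. The larger figures need zero drift. Where drift exists and is modelled, the child-level excess is mostly small. Where it is not modelled, it dominates, and an unstructured student covariance alone does not cure it.

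Finally, the absolute change is modest. In the 85% attendance cases with decay, the 95% half-width grows by 1.96×(0.0135 − 0.0121) = 0.003 to 1.96×(0.0246 − 0.0192) = 0.011, against a target of 0.13. An estimate near the target would be read the same way. The error matters for small observed differences.

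**Conclusion.** The concern holds conditionally. On the plain reading of the model, any fall in within-child correlation with the gap makes the primary standard error too small. With no school-by-year drift, type I error runs from 5% (flat) through about 7–8% (slight decay) to about 14% (stronger decay), so nominal 95% intervals cover about 86–95%. With drift present and modelled, it is about 5–8%. These sizes rest on assumed correlations and attendance, random intercepts only, independent residuals and model-based standard errors. The stated 83% power is not in question. The remedy is cheap and this is the primary test, so the change should be made.

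**What to change.** Keep the stated fixed effects and the school random effect. Then do one of two things, fixed before any outcome data are seen:

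- Replace the student random intercept by an unstructured within-student covariance over baseline and years 1, 2 and 3, with heterogeneous Toeplitz as the fallback if it does not converge.
- Base the year-3 test and interval on standard errors clustered by school, with a small-sample correction for about 22 schools. This is the more robust choice, because it also protects against school-level drift.

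The cost is a sentence in the analysis section or analysis plan and a change of model option. The unstructured form has 10 child-level covariance parameters instead of 2, which a sample of several thousand children can support. The interval will be somewhat wider if the correlation decays; if it is flat, little is lost. The article reports that recruitment and data collection had not begun, so the choice could still be made in advance.

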In the face of low implementation capacity and competing priorities (such as responding to COVID-19) and increasingly obesogenic environments (such as advertising of unhealthy food) [28,29] we contend that communities, and particularly schools, need implementation support to sustain healthy environments. Working with school communities rather than whole communities may help focus implementation support and minimise competing priorities. Also, the Lancet Commission encourages greater application of expert-facilitated (not owned) implementation [20]. Our research has demonstrated it is possible to create environments that protect children from obesity and others have shown that healthy weight can persist after children have participated in school-based interventions [30,31]. However, there is a paucity of research exploring whether system-wide changes to school environments can be sustained so that successive cohorts of children are protected from unhealthy weight gain.

The primary objective of this study is to protect primary school children in rural Victoria, Australia, from unhealthy weight and test implementation strategies for sustaining school environments that promote health and wellbeing. The research questions being addressed in this study are: (1) can Victorian school communities be supported to prevent unhealthy weight gain for 3 years and; (2) what are the optimal implementation strategies to support delivery and maintenance of the intervention in schools? It is hypothesised: (1) a reduction of 0.13 units in z-BMI will be achieved in intervention schools relative to controls after 3 years of intervention and; (2) that implementation strategies will be cost-effective, acceptable, utilised, appropriate, feasible, delivered as intended and maintained in intervention schools.

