### Control

Control schools will receive the usual support available to Victorian schools including the Vic Kids Eat Well initiative introduced by the Victorian state health department [42] in 2022, aimed at establishing healthier food environments for children, along with the Victorian Healthy Schools Achievement Program [43]. This program is designed to aid schools in defining and attaining benchmarks related to healthy eating, physical activity, and mental well-being and may include health promotion support. Control schools will be provided with a written report summarising overweight/obesity prevalence, HRQoL, dietary behaviours, physical activity and sedentary behaviours, oral health, sleep, and the school environment at baseline, after each time-point of data collection, and at the end of the trial. At the end of the trial, they will also receive a report on the overall results of the STAIR trial and, should they wish to design their own intervention actions, access to the STICKE training modules and STICKE software.

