#### Secondary intervention effectiveness outcomes.

Secondary outcomes include overweight/obesity prevalence of grade 1–6 children, captured at the same four time points, and health behaviours of children in grades 4–6 collected via a self-completed questionnaire on electronic tablets [Samsung Galaxy A9+]. Questionnaires will be completed by classes of children in one school period (~ 45 minutes). The questionnaire will ask about physical activity (self-reported time in moderate to vigorous physical activity, use of active transport to and from school), sedentary behaviour (self-reported screen time for entertainment), diet (intake of vegetables, fruit, water, takeaway foods, sweet snacks, savoury snack and sugar-sweetened beverages), oral health (brushing frequency, oral health, dental care access), sleep (self-reported usual sleep and wake times) and HRQoL (global, physical and psychosocial domains) using validated tools (Table 3) [22,25]. Demographic data will include age, gender, country of birth, and ethnicity. The Index of Community Socio-Educational Advantage (ICSEA) [46] will be used to describe children’s socioeconomic position.

**Table 3 pone.0325853.t003:** Primary and secondary outcomes of interests and proposed instrument/measure in supplementary.

Item	Outcome(s) of interest	Proposed Instrument/measure
**Anthropometry** **(objective)**	• Change in z-BMI score (Primary outcome 1) • Change in overweight and obesity prevalence [47]	Height and weight.
**Physical activity and Sedentary behaviour** **(student self-report)**	• Change in the proportion of participants meeting the Australian 24-Hour Movement Guidelines for Children and Young People (5–17) [48] • Change in the percentage of students taking active transport to and/or from school.	Questionnaire containing modified items from the Core Indicators and Measures of Youth Health [49] and SHAPES [50] surveys.

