
#### School-level implementation outcomes.

Each year of the study, the school principal (or nominee) will be invited to complete a school environment audit questionnaire in Qualtrics about their school’s physical activity, healthy eating and well-being policies, practices (i.e., minutes/week devoted to formal physical education/organised sport, canteen menu) (Table 3). In addition, the questionnaire will be used to assess change in frequency, length and attendance numbers of committee meetings providing guidance on the development of policies and practices concerning physical activity, healthy eating, wellbeing and/or mobile phone use (Table 3).

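### School environment change is listed among the outcomes and audited yearly in both arms, but the plan gives no between-arm estimate with an interval for it

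*Protocol article*

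**What the plan says.** The Introduction gives a two-part primary objective. The second part is to "test implementation strategies for sustaining school environments that promote health and wellbeing". Hypothesis 2 then says that the implementation strategies will be, among other things, "appropriate, feasible, delivered as intended and maintained in intervention schools".

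The audit is yearly. Under School-level implementation outcomes: "Each year of the study, the school principal (or nominee) will be invited to complete a school environment audit questionnaire". That sentence does not restrict it to one arm. The Control section says that control schools receive a written report whose topics end with "sleep, and the school environment at baseline, after each time-point of data collection, and at the end of the trial", which implies audit data from control schools too.

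Table 3 is captioned "Primary and secondary outcomes of interests and proposed instrument/measure in supplementary". Its environment row lists change in the policy, physical, economic and socio-cultural environment, followed by many nutrition and physical-activity items.

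The Statistical analysis section assigns secondary outcomes to a generalised linear mixed model. It closes with a different rule for the audit: "The environmental audit, and implementation outcomes will be analysed at the school level using descriptive statistics and thematic analyses".

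**The concern.** Two parts of the article classify the same measure differently. By its place in Table 3, environment change is an outcome to be compared between arms. By School-level implementation outcomes and the last sentence of Statistical analysis, it is an implementation measure to be described.

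The second classification is the one that fixes the analysis, and it provides no contrast, model or interval. This matters more for the audit than for the Table 4 indicators. Those mostly concern intervention schools and their partners, so for them there is no randomised comparator to use. The audit has one.

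The Control section names two statewide programs, Vic Kids Eat Well and the Achievement Program, as part of usual support for Victorian schools. Environments may therefore improve in both arms for reasons unrelated to STAIR. The randomised contrast is what separates the two sources of change. It is also the first thing a reader will want when interpreting the z-BMI result, whichever way that falls.

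**Working it through.** **1. Classification, side by side.**
- Table 3 (caption and environment row): among primary and secondary outcomes, expressed as change.
- Secondary intervention effectiveness outcomes (body text): names overweight/obesity prevalence and child health behaviours, not the environment.
- School-level implementation outcomes: the audit is placed here.
- Statistical analysis: mixed model for secondary outcomes, description for the audit.

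The caption and the analysis rule do not agree.

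**2. Number of items.** The Table 3 environment row has 7 general entries, 8 nutrition bullets, 37 numbered nutrition entries and 7 physical-activity bullets: 7 + 8 + 37 + 7 = 59, with numbered entry 22 repeating entry 18. The article names no summary score.

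**3. The plan's own power figure.** The only one is 83% for z-BMI, from 22 schools, about 200 students each, difference 0.13, SD 1.1, ICC 0.02, baseline measure, exchangeable correlation, α = 0.05 (two-sided assumed).
- Variance of a school-period mean: v = 1.1² × (0.02 + 0.98/200) = 0.03013.
- Covariance between periods: c = 1.1² × 0.02 = 0.0242, so r = c/v = 0.803.
- SE = √[(2/11) × 0.03013 × (1 − 0.803²)] = 0.0441.
- Power = Φ(0.13/0.0441 − 1.96) = 83.9%.

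The stated figure reproduces. It says nothing about the audit, for which no power or precision is given.

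**4. What a school-level contrast on the audit could deliver.** Inputs from the article: 28 schools recruited, 1:1 allocation, 20% school dropout (28 × 0.8 = 22.4, taken as 22), so 14 or 11 per arm. Assumed, because the article gives no value: the correlation ρ between baseline and year-3 score. Differences are in between-school SD units.
- SE = √[(2/k)(1 − ρ²)], with k schools per arm.
- 95% half-width = t × SE, with 2k − 3 df (2k − 2 without baseline adjustment).
- Detectable difference at 80% power, two-sided 0.05, from the noncentral t distribution.

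Example, k = 11 and ρ = 0.5: SE = √(0.1818 × 0.75) = 0.369; half-width = 2.093 × 0.369 = 0.77; detectable difference 1.09.

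| ρ | k = 11: detectable | k = 11: half-width | k = 14: detectable | k = 14: half-width |
|---|---|---|---|---|
| 0 (unadjusted) | 1.26 | 0.89 | 1.10 | 0.78 |
| 0.5 | 1.09 | 0.77 | 0.95 | 0.67 |
| 0.8 | 0.76 | 0.54 | 0.66 | 0.47 |

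A normal approximation at ρ = 0.5 (2.8 × SE) gives 1.03 and 0.92, slightly optimistic with so few schools.

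**5. Single yes/no items.** With Fisher's exact test and 11 schools per arm, a control proportion of 20% needs about 84% in the intervention arm for 80% power, and 30% needs about 92%. From 50%, 80% power cannot be reached. With 14 per arm the figures are about 78%, 87% and 98%. Item-by-item testing is not useful; a summary score with an interval is feasible.

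**The case against.** The best defence is that the choice is deliberate and proportionate. Hypothesis 2 frames maintenance within intervention schools, and no between-arm hypothesis about the environment is stated. Trial design and status calls this a type-1 hybrid (Strengths and limitations says type-2). In a type-1 hybrid, powering and modelling the health outcome while describing implementation is normal. With 22 to 28 schools and dozens of items, description is restrained. Principals are only invited to respond, so numbers may be smaller still. A modelled difference on self-reports from unblinded schools would not remove reporting bias. Scoring rules may also belong in an analysis plan that is not shown.

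Much of this stands. It supports describing Table 4 and single audit items, and labelling any contrast exploratory. It does not explain why a two-arm measure listed in Table 3 has no comparison. Nor is the method merely left to a later document: the article states it.

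Three stronger readings are tempting and are not supported:
- *The trial will be unable to say whether environments changed or lasted.* Yearly summaries by arm from randomised schools would show direction, rough size and persistence. Only the pre-specified contrast and its uncertainty are missing.
- *The audit will be described in the intervention arm only, so statewide programs would pass for STAIR effects.* The within-group analysis appears under Implementation outcomes and concerns intervention school communities. Statistical analysis does not restrict the audit to one arm, and participation in both statewide programs is itself an audit item.
- *Favourable items will be picked out.* The long list leaves room for that, but nothing in the article shows an intention to do it, and no confirmatory claim is attached to the audit.

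**Conclusion.** The point holds in a limited form. The article classifies school environment change in two incompatible ways. The classification that governs the analysis yields no pre-specified between-arm estimate with uncertainty for something that its primary objective sets out to sustain. Without that estimate, change due to STAIR cannot be formally separated from change due to programs open to schools in both arms.

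The z-BMI analysis is untouched. This is a worthwhile improvement, not a threat to the trial's main conclusion.

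The gain is modest: a contrast would detect about 0.95 to 1.09 between-school SD at ρ = 0.5, and about 0.66 to 1.26 SD over the range in the table. These figures assume a roughly continuous summary score, complete audits from 11 or 14 schools per arm, and correlations that the documents do not supply. The article gives no expected size for environment change, so it cannot be said whether effects of that order are plausible. That coverage of control schools is complete and yearly is inferred from the reports promised to them.

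**What to change.** 1. Reconcile Table 3 with School-level implementation outcomes and Statistical analysis, stating whether environment change is a secondary outcome or an implementation measure, and that the audit covers both arms.
2. Before data collection, which the article says has not begun, name one or two summary environment scores, for instance one for nutrition and one for physical activity, as far as the audit tools allow. Whether they yield usable scores cannot be judged from the article.
3. Report the year-3 between-arm difference in each score with a 95% CI from a school-level linear regression adjusted for the baseline score, labelled exploratory. Add the randomisation stratum only once it is properly defined: Randomisation and blinding procedure names only enrolment of 120 or more, and Setting and recruitment already excludes smaller schools, so the text describes a single stratum.
4. Keep single items descriptive, shown by arm and year.
5. State with the result that the audit is self-reported by unblinded schools.

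The cost is one short regression per score on data already being collected, plus the work of fixing the scores in advance. The drawback is a wide interval, with a half-width of about 0.5 to 0.9 SD over the assumed range, which must not be read as evidence of no effect.
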